### **Laboratory Test Results**

All laboratory values must be reviewed and appraised by the investigator or research personnel for clinical significance. For any abnormal laboratory value considered to be new since baseline and clinically significant, details must be provided on the Laboratory Adverse Event case report form. This will include whether the event is considered serious, the relationship to the MSCT or MRI contrast agent or other agents, the action taken, and patient outcome. Significant abnormal values occurring during the study are to be followed until repeat values return to normal, stabilize, or are no longer considered clinically significant.

### **Clinical Adverse Events**

All clinical adverse events will be recorded on the Adverse Events (AE) page of the CRF with details including seriousness, date of occurrence, intensity, time of onset/stop, relationship to study (drug, contrast, procedure), action taken (with respect to study-related drug or study-related procedure only), and patient outcome.

**Serious Adverse Events**

Serious adverse events will be recorded and classified according to the following categories.

1. Fatal;
2. Is life threatening?
3. Results in persistent or significant disability or incapacity
4. Is a congenital anomaly or birth defect?
5. Requires inpatient hospitalization or prolongation of existing hospitalization with the following exceptions:
  - a. Preplanned (prior to study), unless hospitalization is prolonged
  - b. Ambulatory treatment units or <24 hour re-hospitalizations
  - c. Hospitalization for elective procedure
  - d. Emergency room visit.

The procedure of reporting of Serious Adverse Events following MSCT is as follows:

1. Report any serious adverse events to the coordinating investigator within 24 hours of knowledge of event.
2. Report any serious adverse event to the IRB according to the local IRB procedures.
3. Complete appropriate Event Form for any complication and/or serious adverse events.
4. Attach physician /nurse notes or summaries regarding the event of to the Event Form.
5. Report of a patient death must be accompanied by a brief statement of the pertinent details, the death record, death certificates, and autopsy report (if performed).

---

## 11 Statistics

Since the benefit of the non-invasive technology, if it exists, should not be withheld from potential beneficiaries for unreasonably long time, and on the other hand the technology might infiltrate medical practice without scientific evidence of benefit, if trial time is too long, it was agreed to aim at a study size allowing for getting results within a 2 years period. Power should be at least 80% with a type I error of  $\alpha = 0.05$  (two-sided).

The primary objective of this study is to analyze the diagnostic accuracy of MSCT using 320 simultaneous detector rows for detection of coronary artery in-stent restenoses in comparison to conventional coronary angiography.

We expect a per-patient diagnostic accuracy of combined CTA and CTP of 87% in comparison to conventional coronary angiography. 90 patients are needed to detect these differences with a power of 80% and an alpha level of 0.05.

The statistical design and all statistical analyses will comply with the International Conference on Harmonization (ICH) Guidance for Industry: E9 Statistical Principles for Clinical Trials.

The assumptions for diagnostic accuracy of MSCT are based on the previous studies published (**Table 1**) and the expected improvement using 320-slice CT.

Secondary endpoints will be evaluated using t-tests, Mann-Whitney-U-tests,  $\chi^2$ -tests, or survival analysis according to scaling. Subgroups (gender, age groups, symptoms) will be analyzed exploratively.

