### Secondary Objectives

1. To analyze per-patient sensitivity, specificity, and receiver-operating characteristic curves.
2. To analyze per-stent accuracy, sensitivity and specificity, and receiver-operating characteristic curves. For this analysis a statistical adjustment for clustering of stents within patients will be conducted using nonparametric analysis of variance.
3. To analyze interobserver variability in detection of coronary artery in-stent restenoses using MSCT.
4. To compare diagnostic accuracy for stents in different locations (coronary vessels), of different size and length, and for stents made of different materials.
5. To analyze the influence of different scan (heart rate, heart rate variability) and patient characteristics (gender, age, diabetes, body mass index) on image quality and diagnostic accuracy of MSCT.
6. To compare procedural complications of MSCT and conventional coronary angiography. These complications will include.
  - death,
  - stroke, and
  - myocardial infarction and
  - moderate to severe groin hematoma, groin pain, infections, allergies, thromboses, and arteriovenous fistula or other complications (if prolonging the in-hospital stay significantly [by at least 24 hours]).

- 
7. To analyze the cost-effectiveness using the primary and secondary efficacy data, the QALY data, and cost data derived from the trial.
  8. To analyze patient preference and satisfaction with and comfort during the imaging tests as recently described (Schönenberger et al. PLoS ONE 2007).
  9. To compare the amount of contrast agent and radiation exposure and the room time required (excluding time for interventions) of both tests.
  10. In addition, noncoronary causes of symptoms (e.g. pulmonary embolism, aortic dissection, pericarditis, pleural effusion, pneumonia, or hiatal hernia) will be recorded to analyze whether the cross-sectional imaging capabilities of MSCT might lead to a higher detection rate of those important incidental findings.
  11. To analyze which image quality in MSCT coronary angiography is required to directly reliably triage patients with suspected coronary artery in-stent restenoses.
  12. To analyze the correlation and agreement between MSCT coronary angiography and conventional coronary angiography (using quantitative analysis) for estimation of the percent diameter stenosis.

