### Inclusion Criteria

1. Suspected coronary artery in-stent restenoses based on clinical findings or findings on other noninvasive imaging tests and planned coronary angiography within the next 14 days. This clinical indication will be made by cardiologists. The activities of the cardiologists will be overseen and directed by the Cardiology Investigator of the Trial ([name]). All coronary artery stents (regardless of type and size) will be

---

eligible for inclusion in the trial. No maximum number of stents per patient will be used to exclude patients.

2. Able to understand and willing to sign the Informed CF.

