## **12 Quality Control and Assurance**

### **Methods Against Bias**

Diagnostic accuracy trials are significantly influenced by selection and verification bias. To avoid these biases we will include a consecutive cohort of patients which will thus be representative of patients with suspected coronary artery in-stent restenoses. To avoid verification bias MSCT will always be performed prior to conventional coronary angiography. This way it will be avoided that patients with positive findings on invasive imaging and the clinically driven necessity to perform an MSCT will be included in the trial. Also all patients will undergo conventional angiography regardless of the result of MSCT coronary angiography.

A primary concern is data quality with regard to transcription of original data from the patients' records to the CRFs. Thus the accuracy of every 10th data set will be compared with the original patient's files.

The coordinating investigator will assure the timely collection of complete and accurate data. There are two major steps associated with ensuring that accurate and complete data will be collected: 1) all persons associated with data collection should be properly trained and familiarized with the tasks that they are to perform; and 2) performance of the required procedures should be monitored and large deviations from study norms investigated.

Charité staff will prepare monthly patient recruitment reports showing the number of patients recruited for that week and cumulatively. In addition, a comparison to recruitment goals will be included. These reports allow the study leadership to monitor the recruitment and follow-up efforts. It is important for the statistical precision of the study to recruit all of the patients suggested by the sample size calculations and to obtain as much follow-up data as possible. In addition to the recruitment reports, a quarterly performance report will include information on the number and percent of forms or data delinquent.

Written CRFs will be used to capture data electronically. The data entry system program provides for editing of data, which includes range checking, table look-up for value accuracy, and intra and inter-form logical consistency checks. If an error occurs, the system automatically notifies the user, and if the error cannot be corrected immediately, errors will be printed out in hard copy for resolution by the study data manager.

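### The stated rule for choosing secondary-endpoint tests ignores pairing of CT with angiography in the same patients, and leaves the stent comparisons of objective 4 without a clustering adjustment

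*Protocol*

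**What the plan says.** Protocol Section 11 (Statistics) gives one sentence on secondary endpoints: "Secondary endpoints will be evaluated using t-tests, Mann-Whitney-U-tests", then chi-square tests, "or survival analysis according to scaling". Scale of measurement is the only selection rule. Dependence between observations is not mentioned, and neither the Wilcoxon signed-rank nor the McNemar test is named.

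The design is within-patient. Under Methods Against Bias, CT always comes first and "all patients will undergo conventional angiography regardless of the result of MSCT coronary angiography". Three secondary objectives then set the two procedures against each other:

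- Objective 6: "To compare procedural complications of MSCT and conventional coronary angiography".
- Objective 8: "To analyze patient preference and satisfaction with and comfort during the imaging tests".
- Objective 9: "To compare the amount of contrast agent and radiation exposure and the room time required (excluding time for interventions) of both tests".

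On stents, the inclusion criteria state: "No maximum number of stents per patient will be used to exclude patients". Objective 2 (per-stent accuracy, sensitivity, specificity and ROC curves) promises an adjustment for stents clustered within patients, by nonparametric analysis of variance, and ties it to that analysis. Objective 4 is listed separately, with no such statement: "To compare diagnostic accuracy for stents in different locations (coronary vessels), of different size and length, and for stents made of different materials".

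**The concern.** An analyst who applies Section 11 as written would take Mann-Whitney U for a skewed or ordinal outcome such as room time or comfort, and chi-square for a binary one such as complications. Both treat the CT values and the angiography values as coming from two separate groups of patients. The pairing, which is the main statistical advantage of giving every patient both tests, would be thrown away.

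For objective 4 the same rule leads to a chi-square test on stents, as if two stents in one patient were two independent observations. At stake are the p-values and intervals of the secondary comparisons, not the primary result.

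**Working it through.** **The plan's own figure.** The 90 patients rest on the primary one-sample test (75% against 87%, two-sided 0.05, power 80%):

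n = [(1.96·√(0.75·0.25) + 0.8416·√(0.87·0.13)) / 0.12]² = [(0.849 + 0.283) / 0.12]² = 88.9, so 89.

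The stated 90 reproduces to within one patient. It does not depend on any secondary test.

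**Pairing, shown for means.** Take n pairs, equal standard deviation σ and within-patient correlation ρ. The true variance of the mean difference is 2σ²(1−ρ)/n; an unpaired test uses 2σ²/n. So:

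- ratio of standard errors (unpaired to true) = 1/√(1−ρ)
- true type I error at nominal 5% = 2·[1 − Φ(1.96/√(1−ρ))]

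The protocol gives no ρ, so 0.3 and 0.5 are assumptions.

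| ρ (assumed) | standard error too large by | true type I error |
|---|---|---|
| 0.3 | 1/√0.7 = 1.20, +20% | 1.9% |
| 0.5 | 1/√0.5 = 1.41, +41% | 0.6% |

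A simulation with 90 pairs (10,000 runs per value of ρ) gave 1.8% and 0.7%. For a true difference of 0.3 standard deviations, the power of the unpaired t-test was 52% and 53%, against 67% and 81% for the paired t-test.

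The factor is derived for means. It illustrates the direction for Mann-Whitney U and chi-square but is not their exact size. With rare complications there is little within-patient correlation to exploit, and the effect may be small.

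**Stents per patient.** Two cited studies have both counts in the Background section and its Table 1: 232 stents in 143 patients (1.62) and 102 stents in 64 patients (1.59), or about 1.6. A value of 2 is added as an assumption.

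**Clustering, stent characteristic constant within patient.** Design effect = 1 + (m−1)·ICC; true type I error = 2·[1 − Φ(1.96/√(design effect))]. The intraclass correlation (ICC) is assumed.

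| m | ICC | design effect | true type I error |
|---|---|---|---|
| 1.6 | 0.3 | 1.18 | 7.1% |
| 1.6 | 0.5 | 1.30 | 8.6% |
| 2 | 0.3 | 1.30 | 8.6% |
| 2 | 0.5 | 1.50 | 11.0% |

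**Clustering, stent characteristic varying within patient.** Location, size and length can differ between stents of one patient. In the extreme case of one stent in each category per patient, the comparison is paired and the first formula applies with the ICC in place of ρ: 1.9% and 0.6%. The error then runs the other way.

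**Survival analysis.** No secondary objective and no endpoint in Section 8 is a time to an event. The stated observation is at least 2 days after the procedures. Methods Against Bias mentions follow-up data but defines no follow-up endpoint.

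**The case against.** Several points against the concern are sound.

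- A t-test may be paired. A reader might infer that every test named is for independent samples; the text supports that only for Mann-Whitney U and the ordinary chi-square test.
- Section 11 is one generic sentence and assigns no test to any objective. A statistical analysis plan, not shown, may name the paired forms. This stands as mitigation. But the protocol does fix a selection rule, and scale alone is the wrong rule for paired data.
- Independent-sample tests suit comparisons between different patients, such as accuracy or image quality by gender or diabetes in objective 5. That is right, and they should stay for those.
- Clustering is not ignored: objective 2 handles it, and objective 4 is per-stent accuracy broken down by stent type. The gap is only that the promise is confined to objective 2's analysis.
- Preference in objective 8 is naturally one choice per patient, not a pair of ratings. Only satisfaction and comfort are clearly paired.

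A reader might also infer that the stent comparisons will give intervals that are too narrow. That holds only where the characteristic is constant within patient, and objective 4 begins with location, which need not be. Nor does listing survival analysis show a planned analysis without data: it is one option in a list and, with no such endpoint, would simply not be used.

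**Conclusion.** The point holds as a defect of the secondary analyses. Choosing by scale alone leads to Mann-Whitney U and chi-square tests for comparisons that are within-patient by design (objectives 6 and 9, and the satisfaction and comfort ratings in 8). With positive correlation the consequence is lost power, not false positives: for means, a true type I error of about 1.9% to 0.6% at assumed correlations of 0.3 to 0.5, and possibly little effect for rare complications.

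For objective 4 an unclustered chi-square test is miscalibrated, but its direction depends on the stent characteristic: about 7% to 11% if constant within patient, under the assumed ICC of 0.3 to 0.5 and 1.6 to 2 stents per patient, and possibly below 5% if it varies. The documents give neither correlation, so these figures show plausible size and are not estimates for this trial.

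The primary analysis and the 90 patients do not change. The survival-analysis item alters no result.

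**What to change.** Replace the sentence on secondary endpoints in Section 11 with wording such as:

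> Within-patient comparisons of MSCT with conventional angiography use the paired t-test or the Wilcoxon signed-rank test for continuous or ordinal outcomes and the exact McNemar test for binary outcomes. Preference, recorded as a single choice per patient, is analysed by a one-sample binomial or sign test. All stent-level comparisons, including objective 4 and the stent-level parts of objective 5, use the clustering adjustment of objective 2 or generalised estimating equations. Unpaired tests are used only between different patients.

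As tidying, delete survival analysis or name the endpoint it is meant for.

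The cost is a change of wording in the protocol, carried into the statistical analysis plan. It needs no further patients or data, and it recovers power for the comparisons of CT with angiography.

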## **12 Quality Control and Assurance**

### **Methods Against Bias**

Diagnostic accuracy trials are significantly influenced by selection and verification bias. To avoid these biases we will include a consecutive cohort of patients which will thus be representative of patients with suspected coronary artery in-stent restenoses. To avoid verification bias MSCT will always be performed prior to conventional coronary angiography. This way it will be avoided that patients with positive findings on invasive imaging and the clinically driven necessity to perform an MSCT will be included in the trial. Also all patients will undergo conventional angiography regardless of the result of MSCT coronary angiography.

A primary concern is data quality with regard to transcription of original data from the patients' records to the CRFs. Thus the accuracy of every 10th data set will be compared with the original patient's files.

The coordinating investigator will assure the timely collection of complete and accurate data. There are two major steps associated with ensuring that accurate and complete data will be collected: 1) all persons associated with data collection should be properly trained and familiarized with the tasks that they are to perform; and 2) performance of the required procedures should be monitored and large deviations from study norms investigated.

Charité staff will prepare monthly patient recruitment reports showing the number of patients recruited for that week and cumulatively. In addition, a comparison to recruitment goals will be included. These reports allow the study leadership to monitor the recruitment and follow-up efforts. It is important for the statistical precision of the study to recruit all of the patients suggested by the sample size calculations and to obtain as much follow-up data as possible. In addition to the recruitment reports, a quarterly performance report will include information on the number and percent of forms or data delinquent.

Written CRFs will be used to capture data electronically. The data entry system program provides for editing of data, which includes range checking, table look-up for value accuracy, and intra and inter-form logical consistency checks. If an error occurs, the system automatically notifies the user, and if the error cannot be corrected immediately, errors will be printed out in hard copy for resolution by the study data manager.

Quality assurance procedures will be implemented at every level of this study. A quality assurance procedure will also be implemented in the area of data entry, where certain key fields on each form will be also reviewed a third time by the data manager after processing. A report on quality assurance measures and activities will be prepared every six months for review. This report will include information on protocol violations, missing and delinquent CRF submission.

Original MSCT data as well as conventional coronary angiography films must be maintained and kept for a period of at least 30 years according to the Deutsche Röntgenverordnung (see information in the patient CF).

### **SOPs**

Standard operating procedures (SOPs) will be set up for the following pivotal and decisive aspects and actions during the trial: performance and analysis of MSCT.

## **13 Ethics**

### **General**

The study will be conducted in accordance with the protocol, the current revision of the Declaration of Helsinki, the current guideline for Good Clinical Practice, and with the applicable regulatory requirements. The study protocol will have to be approved by the institutional review boards of each participating center. MSCT exposes the patients to a radiation dose of approximately 15 to 20 mSv. To ensure adherence to legal regulations and safety of the patients, the Federal Department for Radiation Protection will review the study protocol. Iodinated contrast agents will be used for MSCT. These agents have a well-known low risk profile (30). However, these agents will be administered twice for MSCT. Patients will benefit from the detection of noncoronary causes of their symptoms by MSCT.

Due to the importance of protecting study data at the Charité, access to all computer files and programs will be restricted to authorized personnel through the use of passwords and automatic access control at the file level. The Charité intranet has the latest firewall protection and the latest MacAfee virus protection, both of which are updated daily.

### **Time Intervals between Procedures**

MSCT coronary angiography is to be performed within 14 days after inclusion of patients for safety reasons. In no instance this time period is allowed to be delayed. Conventional coronary angiography will be performed within 14 days after MSCT.

### **Institutional Review Board**

The coordinating investigator is responsible for submitting the protocol and Informed Consent Form for the proposed clinical trial to and obtaining approval by the IRB of the Charité. This study is to be conducted according to globally accepted standards of Good Clinical Practice, and in agreement with the latest revision of the Declaration of Helsinki. This protocol and any amendments will be submitted to the properly constituted IRB, in agreement with the local prescriptions, for normal approval of the study conduct.

### **Federal Department for Radiation Protection**

After approval of the study at the IRB of the Charité, the trial protocol and the radiation characteristics of the MSCT scan will be submitted to the Federal Department for Radiation

Protection for review and approval.

### **Modification of the Protocol**

The coordinating investigator must submit necessary protocol modification to the Institutional Review Board and obtain written approval before implementation of any modifications.

## 14 Publication Policy

The coordinating investigator and the trial statistician are responsible for the writing of the manuscript concerning the main objective of the trial. This shall be done within a period of not more than 12 months after obtaining the final data. At least 1 month prior to submission of the manuscript the manuscript draft will be submitted to the other investigators for review and approval. Authors of all the manuscripts generated from the study will need to fulfill all of the following three criteria according to the ICMJE Uniform Requirements for Manuscripts Submitted to Biomedical Journals:

1. substantial contributions to conception and design, or acquisition of data, or analysis and interpretation of data;
2. drafting the article or revising it critically for important intellectual content; and
3. final approval of the version to be published.

Because of the fact that 3 departments are participating in the trial a maximum of two authors will be allowed per department. In addition, the corresponding author, who directly responsible for the manuscript drafting and the independent blinded readers of CT and conventional coronary angiography can be authors on the manuscript.

There will be no intermediate publications on the main objective of the trial. Each department investigator or co-investigator agrees not to publish or present on the outcomes of the study in the patient he/she has included. Secondary objectives of the trial can be published prior to publication of the main objectives of the study provided that the coordinating investigator approves this.

